### Operational framework

#### The intervention

The intervention (oral health education) was provided in the form of individual presentations of about 30 min. Thereafter, a practical demonstration of tooth brushing was presented. Each participant received a carry-home message in the form of a pamphlet containing similar information to the presentation, in the participants’ mother tongue. Apart from brushing, there is information about the primary dentition, dietary habits and their effect on caries and obesity. Bottle feeding and its effect on ECC was emphasized. Moreover, the importance of regular dental visits was highlighted. A pilot study of 20 immigrant parents had been conducted previously, to assess the questionnaire to be used and the intervention to be applied. The control group will be provided with the intervention material after the end of the study.

#### Theoretical framework

Different theoretical approaches are used in this project, including:

MI: defined as “a person-centered counseling style for addressing the common problem of uncertainty about change”. A recent systematic review identified MI as being the most effective approach for altering health behavior in an individual oral health promotion setting [33]. Therefore, it is strategic to use culturally adapted MI to convey actionable information and motivate health-related behavioral change in families with newborn children.

CRFA: This approach addresses risk factors common to many chronic conditions within the context of the broader socio-environmental setting [26]. The main implication of CRFA for oral health policies is collaboration with other sectors and disciplines. Oral health issues need to be integrated into primary health care, with recommendations which promote general health. As some chronic diseases share common causes, adopting a collaborative CRFA is more rational than focusing on one disease.

TPB: is a commonly utilized social cognitive theory, predicting behavioral intention and behavior. TPB incorporates three main constructs that influence behavioral intention, including attitude, subjective norms, and perceived behavioral control. The TPB has successfully accounted for a high proportion of variance in several health-related behaviors including those related to oral health [34]. In this project, we will use the TPB to explain dietary behavior intentions of parents with NW immigrant background and identify the most important causal factors. Dietary intention is predicted by attitudes, subjective norms, and perceived behavioral control. According to the TPB, the effectiveness of educational strategies depends on successfully changing the most important attitudinal components of TPB. The relative weight of the predictors of behavioral intention determines whether the main focus should be on attitudes, subjective norms, or perceived behavioral control.

### Statistical analysis

The data will be analyzed using STATA and SPSS version 24 (SPSS Inc., Chicago, II, USA). Descriptive statistics such as mean and standard deviation for continuous variables and frequency and percentage for categorical variables will be presented. Univariable analysis will be based on cross tabulation and Chi Square statistics. Independent sample t test will be used to assess how sum scores of knowledge, attitudes and the parent’s own oral hygiene and dietary habits varied according to the parents’ age, educational level, and duration of residence in Norway. Differences between intervention and control groups will be analyzed using T-tests and associations will be quantified using eta coefficients. A two-sided significance level of 5% will be applied in all analyses.

Primary analysis will follow an “Intention-to-treat” approach. Comparison between the intervention and control groups at baseline and follow-up to calculate intragroup changes of outcome variables will be performed using generalized linear model (GLM) repeated measures. In the secondary analysis, ‘per-protocol’ approach will be used, where the participants would be excluded if they (1) did not participate in the intervention program, (2) did not complete the questionnaires, (3) were not eligible according to the inclusion and exclusion criteria.

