### Aims

The objectives of this project are:

To investigate the efficacy of a culturally adapted behavioral intervention on knowledge, attitudes, and behaviors related to a child’s risk for dental caries and obesity, with special reference to parents of NW immigrant background, with children aged 0–6 months.To assess the effect of the behavioral intervention on children’s caries increment and family quality of life.To generate research-based information about NW immigrants’ oral health issues, healthcare needs, and utilization of health services.To evaluate possible differences and similarities in oral hygiene and feeding practices among parents of different cultural backgrounds (immigrants and native Norwegians).To monitor parents’ attitudes to their children’s oral health in a follow-up study for children aged 3 and 5 years and to measure the children’s quality of life, body mass index (BMI) and caries status.

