### Data collection and assessment

#### Data collection instrument

Data will be collected in both phase I and phase II, using a questionnaire intended to elicit parental information about caries and obesity risk behaviors as well as behavioral determinants that will be targeted during the intervention.

The ***first*** part of the interview schedule will assess demographics and socioeconomic status. Demographic data include age, gender, and indicators of socioeconomic and migration status: father’s-mother’s education, occupation, and years of residence in Norway. The ***second*** part of the interview schedule will include parental *knowledge related to* breastfeeding, healthy feeding practices, etiology and prevention of obesity, and dental caries, *attitudes* (food habits, tooth cleaning, regular dental visits), eating habits (sugary food/drinks intake, frequency of consumption of sweet beverages) and different oral hygiene practices. The theory of planned behavior (TPB) will be operationalized according to the practices of the immigrant parents. The ***third*** part of the interview schedule will include information about the parents’ own oral hygiene and dietary habits, cultural traditions, perceived oral health and the utilization of general/dental health services. Finally, the Early Childhood Oral Health Impact Scale (ECOHIS) will be used to measure the quality of life of the children and their families. The ECOHIS is a tool used to analyze the impact of oral health issues on the quality of life of families with children aged between 3 and 5 years [32].

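### Sum scores are to be related to parents' age, education and years of residence by independent-samples t-tests, which force two-group splits at unstated cut-points and leave each association unadjusted

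*Protocol article*

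**What the plan says.** The Statistical analysis section names the test and the factors: "Independent sample t test will be used to assess how sum scores of knowledge, attitudes" and the parents' own oral hygiene and diet "varied according to the parents’ age, educational level, and duration of residence in Norway". It gives no cut-points and no grouping of education.

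Under Data collection instrument, the first part of the interview covers age, gender and "education, occupation, and years of residence in Norway". Residence is therefore recorded as a number of years. The unit for age and the categories for education are not given.

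Two other methods in the Statistical analysis section could bear on the point:
- "Univariable analysis will be based on cross tabulation and Chi Square statistics", which is again one factor at a time.
- The repeated-measures model: the comparison of intervention and control groups "will be performed using generalized linear model (GLM) repeated measures". No parental characteristics are listed for it.

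On the error level, "A two-sided significance level of 5% will be applied in all analyses".

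The second half of the Aims opens the descriptive purpose: "To generate research-based information about NW immigrants", followed by their oral health, care needs and use of services.

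**The concern.** The article fixes a test that does not suit the predictors as collected. An independent-samples t-test has a two-valued grouping variable. A number of years can enter only after it is split, and so can age if it is recorded in years. This has three consequences:

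- **Lost information.** Parents on the same side of the cut are treated as alike, however far apart they are.
- **A free choice of cut.** With no cut-point stated, the result can depend on one chosen after the data are seen.
- **No adjustment.** Age, education and time in Norway are plausibly correlated among immigrant parents. Tested singly, one can stand in for another. Centre is ignored too, although the Sample size section gives health stations a random effect and the Randomization section makes health centres the sampling unit.

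The Discussion itself warns that differing lengths of residence may affect comparisons and acculturation. At stake is the precision and meaning of those descriptive results, not the estimate of the intervention effect.

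**Working it through.** The article states no figure for these tests, so there is nothing of its own to reproduce. Everything below rests on stated assumptions.

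**Inputs from the article.** Two-sided 5% level (Statistical analysis); planned minimum N = 300 (Sample size); N = 475 in 7 centres (Fig. 3 caption); residence in years (Data collection instrument).

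**Assumed inputs.** Shape of the predictor, position of the cut, a linear relation to the score, and the correlations. Clustering is ignored in the power figures.

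**1. Information kept by a split.** This is the squared correlation between the predictor and its two-group version. For a normal predictor cut at proportion p it is φ(z_p)² / [p(1 − p)], where φ is the standard normal density. At the median it is 0.3989² / 0.25 = 2/π = 0.637, a loss of 36.3%. So 300 parents act like 300 × 0.637 = 191, and 475 like 302.

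**2. Other cuts and shapes.**

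| Predictor | Split | Loss |
|---|---|---|
| Normal | 50/50 | 36% |
| Normal | 60/40 | 38% |
| Normal | 70/30 | 42% |
| Normal | 80/20 | 51% |
| Normal | 90/10 | 66% |
| Uniform | median | 25% |
| Gamma, shape 2 | median | 45% |
| Exponential | median | 52% |
| Lognormal, sigma 0.75 | median | 60% |

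The non-normal rows were simulated with 2 million draws.

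**3. Education.** With equally common, linearly scored levels, the loss is 0% if there are two levels, 25% with three, 20–40% with four and 25–50% with five, depending on the cut.

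**4. Power.** By the Fisher z approximation, power = Φ(atanh(r)·√(N − 3) − 1.96). A median split of a normal predictor shrinks r by √(2/π) = 0.798. For an assumed r = 0.15 the split correlation is 0.15 × 0.798 = 0.120.

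| N | Continuous | Median split |
|---|---|---|
| 300 | Φ(0.151 × 17.23 − 1.96) = 74% | Φ(0.120 × 17.23 − 1.96) = 55% |
| 475 | Φ(0.151 × 21.73 − 1.96) = 91% | Φ(0.120 × 21.73 − 1.96) = 74% |

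For 80% power at r = 0.15, N = [(1.96 + 0.8416)/atanh(r)]² + 3, which is about 347 with the continuous predictor and 546 after the split.

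**5. One factor standing in for another.** Assume age and residence correlate 0.5 and only residence is related to the score, with r = 0.2. Age then has a correlation of 0.5 × 0.2 = 0.10 with the score, with no association of its own. In 4,000 simulated data sets of N = 300, the median-split t-test on age rejected in 27%. The test of age in a regression that also held residence rejected in 4.5%, close to the nominal 5%.

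**The case against.** The strongest case against has four parts.

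- **The size of the loss.** A reader might infer that about a third of the information is lost for all three factors. The article does not support that. It names no median split, distribution or cut-point, so the 36% belongs to one assumed case. This objection stands, and the loss is given here only as a range.
- **Education.** A reader might also infer that education must be collapsed. Its coding is not stated. If it is recorded in two levels, a t-test loses nothing. This stands.
- **Adjustment.** The article does not say that the t-tests are the only analysis of these associations, and a fuller plan may add a multivariable model. So the lack of adjustment is a property of the named test; it does not show that no adjusted analysis is planned. The correlation between age and residence is likewise an assumption. This limits the claim but does not remove it: the t-test is a stated choice, and the article describes no other analysis for these associations.
- **Importance.** None of the listed primary or secondary outcomes depends on these tests, and their link to the descriptive aim is loose, since that aim goes on to health issues, needs and service use. This stands and keeps the point minor.

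**Conclusion.** The concern holds as a minor point. The named test cannot use years of residence as recorded, nor age if it is in years, without a split at an unstated cut. It also tests each factor unadjusted for the others and for centre.

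The size is conditional. For age and residence, a loss of 25–60% covers the shapes examined when split at the median, and very uneven cuts of a normal predictor reach about 66%. For education it can be nil. The power falls of about 19 percentage points at N = 300 (74% to 55%) and 17 at N = 475 (91% to 74%) rest on an assumed correlation of 0.15, a normal predictor, a median split, a linear relation and independent parents.

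A reader should not conclude that the comparison of intervention and control is weakened. These tests do not enter it.

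**What to change.** In the Statistical analysis section, replace the t-tests on parental characteristics with one linear regression per sum score. Enter:
- age and years of residence as continuous terms, with a check for curvature;
- education in its recorded categories;
- centre as a fixed effect.

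A fixed effect is the better choice here because there are only six centres (Sample size) or seven (Fig. 3 caption), too few to estimate a centre variance well. Report adjusted coefficients with 95% confidence intervals.

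The cost is a little more analysis work. All three characteristics are already in the questionnaire, and the named software (STATA, SPSS) fits the model. A reader might assume that the data are already complete, but Trial Status says recruitment was continuing at submission. The change needs no new data items either way.

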## Methodology

### Trial Design

This is a cluster randomized controlled intervention follow-up study. By integrating primary health care and the public dental health service, the basis of the study is the application of an early-life intervention program among parents/children of immigrant backgrounds, using the MI technique and CRFA to prevent dental caries and obesity, thereby improving their general health, oral health, and quality of life. Primary care health centers in the municipality of Bergen, Norway, were randomly allocated to intervention or control groups (allocation ratio 1:1), to evaluate the efficacy of the culturally adapted dietary/hygiene advice. The intervention group received guidance on diet/hygiene and the control group received standard care, including regular health information at the primary care health centers. The study has been funded by the Norwegian Research Council for three years.

The study has two phases:

**Phase I (The Intervention Study)** involves assessing oral health-related knowledge, attitudes, and behavior among immigrant parents of infants (0–6 months). It also involves investigating the potential of a culturally adapted oral health education intervention to prevent the development of ECC and to improve parental oral health-related knowledge and awareness (Fig. 1).

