**Fig. 3 Fig3:**
[figure not shown]
Consort diagram. This figure illustrates the study design (RCT). A total of 7 health centers having 475 participants with children 0-6 months were randomized to an intervention arm and a control arm. RCT, randomized controlled trial

While parent and child waited for the recommended time before discharge after vaccination, an experienced dental professional researcher explained the purpose of the study and provided participating immigrant parents (IM) with the interview schedule. The intervention group received additional information on oral hygiene, modifying dietary risk behaviors, and dietary guidance, while the control group received the regular health information provided at the primary care centers.

Strategies to promote retention include provision of health information. The family was issued with a toothbrush for the child and a plastic mouth mirror for the parent to check the oral cavity.

The child included in the study was referred for dental treatment if needed (the child’s first routine visit to the dentist is at 3 years of age). Reminders about upcoming interviews were sent to the participants and confirmed by telephone.

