### Sample size

Statistical power (+/- 95% CI) to detect a fixed effect the size of 0.15 or 0.25 (left and right panels, respectively) and with a random effect of clusters (health stations), measured in standard deviations, was set to 0.1 or 0.25 (top and bottom panels, respectively). Power was calculated over a range of sample sizes using the power Curve function from the *simr* R library. The number of clusters (health stations) is six, i.e., three per treatment group. Each data point and associated confidence interval are estimated from 1000 Monte Carlo simulations. The results indicate that a total sample size of at least 300 participants (approximately 50 parents/child pairs from each center) is needed to ensure adequate power, given that the effect size is no smaller than 0.25 (Fig. 4).

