### Randomization

Health centers in the municipality of Bergen (i.e., health centers agreeing to participate in the study) were randomly allocated to intervention or control groups by researchers involved in the study. Instead of randomization of individuals within health centers, cluster randomization of the primary sampling unit (health centers) was deemed necessary to avoid contamination of information from those in the intervention group to those in the control group while sharing the waiting room of the same health centers.

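### Health centres are randomised, but the arms are compared with parent-level t-tests and GLM repeated measures, so standard errors are understated and the 5% level is not assured

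*Protocol article*

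**What the plan says.** All references are to the protocol article.

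- **Randomization:** the health centre is the unit of allocation: "cluster randomization of the primary sampling unit (health centers) was deemed necessary to avoid contamination". Trial Design gives the "allocation ratio 1:1".
- **Sample size:** power was simulated "with a random effect of clusters (health stations), measured in standard deviations, was set to 0.1 or 0.25". The section adds: "The number of clusters (health stations) is six, i.e., three per treatment group". It concludes that at least 300 participants, about 50 per centre, are needed for an effect of at least 0.25.
- **Fig. 3 legend:** the count differs: "A total of 7 health centers having 475 participants with children 0-6 months were randomized to an intervention arm and a control arm".
- **Statistical analysis:** on the comparison of arms, "Differences between intervention and control groups will be analyzed using T-tests and associations will be quantified using eta coefficients". The comparison of baseline with follow-up "will be performed using generalized linear model (GLM) repeated measures". All tests are at a two-sided 5% level.
- **Outcomes:** both primary outcomes (parental knowledge and parental behaviour) are changes between the first questionnaire and follow-up. The 24-month caries examination is also compared between arms. It has no baseline, because no teeth have erupted at 6 months.

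No section mentions a centre term, a cluster-robust variance, a cluster-level test or a small-sample correction for the analysis.

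**The concern.** Parents at one centre share staff, catchment area and social background. The Screening and recruitment process section itself says that the centres have different uptake areas. Their responses are therefore likely to be correlated. When centres are randomised, the uncertainty of the arm difference comes largely from how much centres differ, and only six or seven centres inform it.

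A t-test on parents treats some 300 to 475 responses as independent. GLM repeated measures allows for two responses from the same parent, but not for parents of the same centre. The planned analysis thus conflicts with both the unit of randomisation and the model used to size the trial.

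At stake is the error rate of the between-arm tests. A significant result could reflect chance differences between a handful of centres.

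**Working it through.** **Inputs from the article.** Cluster SD s = 0.1 or 0.25; six centres (three per arm) of about 50 parents; alternatively seven centres with 475 parents, so m = 475/7 = 67.9 on average; two-sided alpha 0.05; effect 0.25.

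**Assumptions.** Residual SD 1 (the text gives none), centres of equal size, and for seven centres a split of three and four.

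**1. The plan's own figure.** N = 300 cannot be strictly reproduced, because the text states neither the target power nor the residual SD, and Fig. 4 is not available here. With residual SD 1, effect 0.25 and 150 per arm, power ignoring clustering is 58%. The residual SD used by the authors may therefore differ from 1.

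**2. Type I error of a parent-level t-test on a single-time score.**

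ICC = s²/(1 + s²); design effect DE = 1 + (m − 1) × ICC; true type I error = 2 × [1 − Φ(1.96/√DE)].

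| Centres | s | ICC | DE | Formula | Simulation |
|---|---|---|---|---|---|
| 6 × 50 | 0.1 | 0.0099 | 1.49 | 10.8% | 10.6% |
| 6 × 50 | 0.25 | 0.0588 | 3.88 | 32.0% | 32.2% |
| 7, 475 parents | 0.1 | 0.0099 | 1.66 | 12.8% | 13.0% |
| 7, 475 parents | 0.25 | 0.0588 | 4.93 | 37.7% | 37.9% |

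Example, first row: ICC = 0.01/1.01 = 0.0099; DE = 1 + 49 × 0.0099 = 1.485; 1.96/√1.485 = 1.61; two-sided tail 10.8%. The simulation used 8,000 trials per row (68 per centre for seven centres). With no centre effect the t-test gave about 5%. A t-test on centre means stayed between 4.7% and 5.2% in all these settings.

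**3. Sensitivity to the assumed residual SD.** Changing the residual SD changes the ICC. For m = 50 and 68 the formula gives:

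- ICC 0.005: 7.9% and 9.0%
- ICC 0.02: 16.4% and 20.0%
- ICC 0.05: 29.1% and 34.7%

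At s = 0.1, an ICC of 0.005 corresponds to a residual SD of about 1.41, since 0.01/0.005 = 2.00 = 0.01 + 1.99. A residual SD below 1 would make the inflation larger.

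**4. The change contrast (time by group).** A centre effect that is constant over time cancels from change. What remains is centre-by-time variation. If its SD at each wave is c and the SD of change is 1 (assumed), the centre SD of change is √2 × c. Simulated type I error of the parent-level test:

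| c | 6 × 50 | 7 × 68 |
|---|---|---|
| 0 | 5.1% | 5.2% |
| 0.05 | 8.3% | 10.0% |
| 0.1 | 15.8% | 19.2% |
| 0.25 | 44.6% | 49.9% |

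The article does not state c.

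**5. What a valid analysis costs, 6 × 50.** SE = √[(s² + 1/50) × (1/3 + 1/3)], which is √(0.03 × 2/3) = 0.141 for s = 0.1 and √(0.0825 × 2/3) = 0.235 for s = 0.25. With 4 df, power for effect 0.25 is about 28% and 13%. A 95% interval is (2.776/1.96) × √DE times as wide as the naive one: 1.73 and 2.79 times.

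**The case against.** **The article condenses a fuller plan.** A centre term might be in an unseen analysis plan. That would excuse silence, but the article is not silent: it names parent-level methods and assigns them to the arm comparison. If a fuller plan does it correctly, the published text still conflicts with it.

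**The primary outcomes are changes.** This stands, and it limits the point. A reader might infer that the 11% to 38% figures apply to the primary outcomes. They do not follow from the article, because they describe a single-time score that carries the whole centre effect. For change the inflation depends on centre-by-time variation, which is not given, and could be nil. That protection is absent from a t-test at follow-up and from the 24-month caries comparison.

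**The residual SD of 1 is assumed.** This also stands. The percentages are illustrations, not predictions, and could be lower or higher.

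**Other stronger readings that the article does not support:**

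- That chi-square tests compare the arms. They are listed under univariable analysis and not tied to the arms. The independent-sample t-test sentence likewise concerns parents' age, education and residence.
- That planned confidence intervals are too narrow. The Statistical analysis section plans none, although any taken from these models would be too narrow.
- That the estimate is biased. With randomised centres the fault lies in the standard error.
- That all secondary outcomes are affected. Caries increment from 3 to 5 years, BMI and quality of life compare immigrant with Norwegian families, which is not the randomised contrast.

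**Conclusion.** The point holds as a mismatch between design and stated analysis. Centres are randomised and the trial is sized with a centre effect, but the arms are compared with methods that ignore it. Standard errors are understated wherever centre effects enter the contrast, and the stated 5% level is not assured.

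For single-time comparisons the inflation is material at both planning values, from about twice the nominal level to more than six times (residual SD 1 assumed). Even at an ICC of 0.005, half the smaller planning ICC, it is 7.9% to 9.0%. For change from baseline the size is unknown: none if centre effects are constant over time, considerable if they drift even modestly. It would go too far to say that the 5% level certainly fails for the primary outcomes. The article gives no ground for assuming that it holds.

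This should be corrected before the between-arm analysis, because it concerns the tests of the primary outcomes.

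**What to change.** For the two primary outcomes and the 24-month caries comparison between arms, replace the t-tests and GLM repeated measures with one of the following:

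- **Mixed model** (linear or generalised) with a health-centre random effect, plus a centre-by-time random effect if repeated measures are kept. Use Kenward-Roger or Satterthwaite degrees of freedom where the model is linear.
- **Cluster-level analysis:** a t-test on centre means, or on centre means of covariate-adjusted residuals, with number of centres minus 2 degrees of freedom (4 for six centres, 5 for seven).

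Report the ICC for each outcome. Do not rely on uncorrected robust standard errors or uncorrected GEE, which remain too liberal with so few clusters. Reconcile six against seven centres, since the degrees of freedom depend on it.

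No new data are needed. The cost is precision: under the assumptions above for six centres of 50, intervals about 1.7 to 2.8 times as wide as the naive ones, and power of about 28% or 13% for effect 0.25. The design already carries this uncertainty and the present analysis hides it, so the article should disclose it.

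### The t-tests and eta coefficients named for the arm comparison leave out the randomised health centres, and eta is unsigned and above zero even with no effect

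*Protocol article*

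**What the plan says.** The first paragraph of the Statistical analysis section, after descriptive statistics and univariable methods, states: "Differences between intervention and control groups will be analyzed using T-tests" and, in the same sentence, "associations will be quantified using eta coefficients". It then sets the error rate: "A two-sided significance level of 5% will be applied in all analyses". The second paragraph gives the primary analysis as intention-to-treat, with a repeated-measures generalized linear model for the arms at baseline and follow-up. Means and SDs are planned for continuous variables. Health centre is not mentioned in either paragraph.

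Elsewhere the article treats centre as essential. The Randomization section makes the health center the unit of allocation. The Sample size section says: "The number of clusters (health stations) is six, i.e., three per treatment group". It simulates power "with a random effect of clusters (health stations), measured in standard deviations, was set to 0.1 or 0.25".

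**The concern.** Eta is the square root of the share of total variance explained by arm. Three properties make it a poor statement of an intervention effect:

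- It cannot be negative, so benefit and harm of equal size look alike.
- Its expected value is above zero when the arms do not differ.
- It is not on the scale of the knowledge or behaviour score.

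The larger problem is shared with the t-test beside it. With two arms, eta is a function of the absolute t statistic, so both treat participants as independent. When three whole centres form each arm, chance differences between centres appear as differences between arms. An intervention that does nothing could then be reported with a significant p-value and an eta that looks like a modest real effect.

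**Working it through.** **Figures in the plan.** The article gives no value of eta, so none can be reproduced. Its total of 300 is used here only as an input. The power target, the residual SD and the coding of the effect are not stated, and the power figure is not shown, so 300 is neither confirmed nor refuted.

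**Inputs from the Sample size section.**
- Six centres, three per arm.
- Total sample: "a total sample size of at least 300 participants (approximately 50 parents/child pairs from each center".
- Effect size 0.25, the value on which the sample-size conclusion rests.
- Centre SD s = 0.1 or 0.25.

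**Assumptions.** Residual SD is 1, and 0.25 is a difference between arms in those units.

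**Eta at the target effect.** For two equal arms, eta = (d/2)/√(1 + d²/4). At d = 0.25 this is 0.125/√1.015625 = 0.124. In reverse, d = 2·eta/√(1 − eta²) returns 0.25. Size is preserved; only the sign is lost.

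**Sign.** With 40,000 simulated trials per setting, true differences of +0.25 and −0.25 give the same mean eta within simulation error: 0.125 and 0.125 without clustering, 0.137 and 0.136 at s = 0.25.

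**Design effect.** ICC = s²/(1 + s²) and DE = 1 + 49·ICC.
- s = 0.1: ICC = 0.0099, DE = 1.485
- s = 0.25: ICC = 0.0588, DE = 3.882

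**No true effect, approximate formulas.** Mean eta ≈ √(2/π)·√DE/√299. The rejection rate of the t-test ≈ 2·[1 − Φ(1.96/√DE)].
- s = 0: mean eta = 0.798/17.29 = 0.046; rejection 5%
- s = 0.1: mean eta = 0.046 × 1.219 = 0.056; 1.96/1.219 = 1.608, rejection 10.8%
- s = 0.25: mean eta = 0.046 × 1.970 = 0.091; 1.96/1.970 = 0.995, rejection 32.0%

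**No true effect, simulation (40,000 trials per setting).**

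| Centre SD | Mean eta | 95th percentile of eta | Mean eta ÷ 0.124 | t-test rejects |
|---|---|---|---|---|
| 0 | 0.046 | 0.113 | 37% | 5.0% |
| 0.1 | 0.056 | 0.138 | 45% | 10.8% |
| 0.25 | 0.091 | 0.221 | 73% | 32.5% |

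**Is this special to eta?** Under no effect, the mean absolute value of an unadjusted mean difference is 0.798·√(2(s² + 0.02)/3). That gives 0.092, 0.113 and 0.187, which is 37%, 45% and 75% of 0.25. These ratios nearly match eta's. The inflation comes from leaving out centre, and replacing eta with an unadjusted mean difference would not remove it.

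**Seven centres and 475 participants.** The Fig. 3 caption gives these counts. With equal centres of about 68 (assumed), DE is 1.66 or 4.93. The same formulas give null mean eta of 0.037 without clustering, and 0.037 × √1.66 = 0.047 or 0.037 × √4.93 = 0.081 with it. Rejection rates are about 13% and 38%. The larger sample lowers eta somewhat but does not repair the test.

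**The case against.** A reader might infer that the primary result will be only a p-value and an unsigned index. The text does not support that. The eta sentence closes a paragraph of descriptive and univariable methods, and the next paragraph gives the primary comparison to the repeated-measures model. Means and SDs are also planned, so direction and a crude difference can be recovered.

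A reader might also infer that eta cannot be set against the 0.25 used for sizing. It can, because the conversion is one-to-one in size.

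It is fair to add that the word for associations is loose, and that the sentence before it concerns scores by age, education and residence, where eta would be an ordinary descriptive index. Eta is a recognised measure, and a condensed article may leave estimates and intervals to an analysis plan that is not shown. The inflation is also mostly a feature of the null: at a true difference of 0.25, mean eta moves only from 0.125 to 0.137, although its 95th percentile widens from 0.217 to 0.299.

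All of this stands, and it moves the weight from eta to the omitted centre. It does not dispose of the point. The article commits itself in one sentence to "Differences between intervention and control groups will be analyzed using T-tests" with eta alongside, and neither can carry a centre term. That is an unsuitable choice that is stated, not a detail left out. For the repeated-measures model, silence about centre could be condensation, so it is not counted as an error in itself, but nothing in the text shows that the model would make good the omission.

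**Conclusion.** The point holds in a limited form. The t-test and eta named for the arm comparison ignore the unit that was randomised, so the 5% level is not kept. It becomes about 11% at a centre SD of 0.1 and 33% at 0.25. Eta adds a smaller fault of its own: it has no sign, and under no effect it averages 0.056 or 0.091 against a target-effect value of 0.124. The higher figures belong to the harsher of the plan's two centre scenarios. All of them rest on a residual SD of 1 and six equal centres of 50. The claim that the intervention effect could not be stated at all goes too far, given the planned means, SDs and repeated-measures model. This is a modest point about reporting, together with a real one about the unit of analysis.

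**What to change.** In the Statistical analysis section, replace the t-test and eta as the statement of the arm difference. Report the between-arm difference in mean score, and the standardised difference, adjusted for baseline score. Give a 95% confidence interval from a model with health centre as a random effect and small-sample degrees of freedom. Keep eta, if wanted, only as a descriptive supplement. Say whether the repeated-measures model includes centre.

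The change is to wording and analysis only; no new data are needed. The cost is wider intervals. For six centres of 50, before baseline adjustment, the centre-based half-width on 6 − 2 = 4 degrees of freedom is 2.776·√(2(s² + 0.02)/3), which is 0.39 at s = 0.1 and 0.65 at s = 0.25. The half-width that ignores centre is 1.968·√(2(1 + s²)/150), about 0.23 in both cases. The extra width reflects uncertainty that is already in the design.
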